### Status of Change

When exploring physical activity, particularly those individuals who are embarking on a new exercise program, understanding an individual’s perspective concerning their status of change will provide critical contextual insights. The current understanding regarding behavior change suggests that individuals need to progress through several changes. The most widely used model is the status of change model, which forms part of the 10-stage transtheoretical model [24]. The status of change model consists of 5 separate stages: *“*(1) precontemplation where no intention to change is intended within the next 6 months, (2) contemplation where change is intended sometime in the future (usually defined as between 1 and 6 months), (3) preparation where change is intended in the immediate future (1 month) and steps are taken to help prepare for change, (4) action where the target behavior has been modified for <6 months, and (5) maintenance that is the stage characterized by temporally robust behavior change extending beyond 6 months” [25]. Individuals are believed to transition progressively through the various stages. They can regress to the previous stages. Perhaps it is not surprising that self-efficacy, a situation-specific construct [26], is believed to change as the individual moves through the status of change [15,25]. We selected the WHO physical activity recommendations as a guideline for this study [27].

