### Recruitment

The study will be advertised on social media, commencing in 2021. This is an entirely virtual, BYOD study design, and interested individuals without any underlying health issues and over the age of 18 years will be invited to download the study app from the Google Play store (Alphabet Inc) and Apple App Store (Apple Inc). Those who are willing to consent to the study and own a Fitbit (Fitbit Inc) will be requested to participate in the study. Once consent is given to participate in the study, participants will be asked to share their Fitbit data. Physical activity, sleep, and heart rate data will be shared using an anonymized token system to ensure that only pseudonymized data are included in the study. Once the individuals provide consent to participate in the study and share their Fitbit data, they will be asked to complete the following assessments: demographics, Type D personality, goal-setting, and self-efficacy questionnaire. They will also be asked to perform decision-making games based on the IGT.

Metrics concerning compliance with each assessment will be quantified. Data will be captured over 12 months. At the end of the study period, participants will be sent a notification to thank them for their participation and a link to where the study results will be shared once available.

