#### Status of Change

To ensure that all participants were able to assess their current activity levels against the same criteria, the WHO physical activity guidance [27] was included in the instructions for the *stages of change* questionnaire. Participants were asked to consider only planned physical activities aimed at improving or maintaining physical fitness and health. Active periods should consist of 150 minutes of moderate-intensity physical activity (such as a brisk walk) in a week or 75 minutes of vigorous-intensity physical activity (such as a jog or run) over the course of a week. Participants will be asked to complete the status of changes questionnaire at the start of the study and 6 months after study commencement (Multimedia Appendix 3 includes details of the stages of change questionnaire and screenshots of the app).

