### Data Analysis and Computational Modeling

This study aims to investigate whether we can predict adherence to self-made fitness goals and identify potential behavioral phenotypes based on the changes in the participants’ responses to a series of validated instruments, including self-efficiency, status of change, and Type D personality, and their behavioral performance on the IGT over 6 months. A range of data analysis techniques will be applied to the collected data to achieve this goal.

We term the results obtained from questionnaires and decision-making tasks as predictor variables, whereas the adherence levels of the participants to fitness goals as target variables for convenience of description. The first problem that must be addressed before predicting and clustering is to quantify both the predictor variables and target variables.

Self-efficiency was measured by an instrument including 18 items using the original 0 to 100 numerical rating scale, where 0 represents *cannot do at all* and 100 represents *high certainty to do.* The Type D personality questionnaire also uses numerical rating scales, although with different ranges from 0 representing *false* to 4 representing *true*. However, for the Status of Change questionnaire, the answers were categorical scales of *yes* or *no*. Thus, the one-hot encoding technique, one of the most common encoding methods in machine learning, will convert the categorical answers to numerical formats.

To evaluate participants’ performance on the IGT, both superficial behavioral variables and underlying cognitive parameters will be summarized and estimated from the behavioral data set. Specifically, 2 parameters will be measured in the behavioral summary analysis. The first parameter will be the total amount of gain by the end of the task, and this parameter will be used to measure the overall performance of the IGT. The second parameter will be the IGT learning scores across the task, that is, the difference between the number of good deck selections and that of bad deck selections across the task, used to reflect the learning process in the task. The 100 trial choices will first be divided into five blocks of 20 trials, each without overlap, and the learning score will be calculated for each block. As a result, 5 variables (learning scores) will be created for this measure.

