Finally, the question arises of how to quantify the target variable, that is, the adherence behavior, given that various types of objective fitness data will be collected. We will mainly rely on the data set of activity patterns and the step counts. According to the WHO physical activity guidelines, to improve or maintain physical fitness and health, active periods should consist of 150 minutes of moderate-intensity brisk walking or 75 minutes of vigorous-intensity jogging or running over the course of a week. If the participant completes this minimum exercise in a particular week, their adherence score for this week will be 1; otherwise, the score is 0. The scores for all weeks will be summed to obtain a total score to represent the overall adherence level of this participant.

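### About half of the 12-month adherence total has already accrued when the month-6 predictors are measured, so the model's accuracy cannot be read as advance identification of who will give up.

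*Protocol article*

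**What the plan says.** All of this is in the Protocol article.

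- **Predictors.** Data Analysis and Computational Modeling states: "We term the results obtained from questionnaires and decision-making tasks as predictor variables". The opening aim of that section is to predict adherence and to "identify potential behavioral phenotypes based on the changes in the participants’ responses to a series of validated instruments". Three questionnaires are named there (self-efficacy, status of change, Type D), together with IGT performance, and the span given is 6 months.
- **Timing of the instruments.** The Assessments subsections give self-efficacy, status of change and Type D at the start and again at month 6. For example: "Participants will be asked to complete the status of changes questionnaire at the start of the study and 6 months after study commencement". The IGT is run once within the first 3 months and again at month 6 (Decision-making Tasks).
- **Target.** A week scores 1 if the WHO minimum (150 minutes moderate or 75 minutes vigorous activity) is met and 0 otherwise. Then "The scores for all weeks will be summed to obtain a total score to represent the overall adherence level of this participant".
- **Length of capture.** Recruitment states: "Data will be captured over 12 months".
- **Model.** Making Predictions and Clustering describes each participant by one vector and applies regression algorithms to it.
- **Purpose.** The Objective, Study Hypothesis and Discussion Overview present the result as a model that identifies people likely to give up, so that support can be targeted to them.

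No section limits predictors to the start of the study, starts the target after the last predictor, or sets a landmark time.

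**The concern.** A change score from start to month 6 does not exist until month 6. By then the first half of the target has happened. An association between that change and the full total may mean that the marker foresees later exercise. It may also mean that the first six months of exercise shaped the marker. The planned regression does not separate the two.

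Two instruments are exposed to the second explanation on the article's own account. Status of change is answered against the same WHO minimum that scores the target, and its action and maintenance stages are defined by how long behaviour has already been changed. On self-efficacy, the Introduction says: "self-efficacy, a situation-specific construct [26], is believed to change as the individual moves through the status of change".

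At stake is what the reported accuracy means. A month-6 measure that only reflects past exercise could appear to support the study hypothesis. A model that needs month-6 inputs would also reach people late, because the article's own background figures put many quitters before that point.

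**Working it through.** The article gives no accuracy, power or effect figure on this point, so there is nothing of its own to reproduce.

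**1. Timeline** (Recruitment; Assessments; Data Analysis and Computational Modeling)

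- Target: about 52 weeks.
- Month-6 predictors: 26/52 = 50% of the target is already observed.
- First IGT, as late as month 3: up to 13/52 = 25% is already observed.
- The phrase "their behavioral performance on the IGT over 6 months" could be read as ending the target at month 6 too. The overlap with the month-6 measures would then be 26/26 = 100%. The point holds on either reading.

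**2. How much stopping falls before month 6** (gym-member figures in Background)

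- First study, 47%, 86% and 96% stopped by months 2, 6 and 12. Share of 12-month quitters gone by month 6: 0.86/0.96 = 90%.
- Active time in the same study, trapezoids under 1, 0.53, 0.14, 0.04:
  - months 0-6: 2 × (1 + 0.53)/2 + 4 × (0.53 + 0.14)/2 = 1.53 + 1.34 = 2.87
  - months 6-12: 6 × (0.14 + 0.04)/2 = 0.54
  - share before month 6: 2.87/3.41 = 84%
- Second study, 47.3% to 56% over a year, constant hazard assumed. Stopped by month 6: 1 − √0.527 = 27.4% to 1 − √0.44 = 33.7%. Share of 12-month quitters: 0.274/0.473 = 58% to 0.337/0.56 = 60%.

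**3. What a purely backward-looking marker would show**

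Let W1 be the score for weeks 1-26, W2 the score for weeks 27-52, and T = W1 + W2. Let the marker be X = r × z(W1) + noise, so that it holds nothing about W2 beyond W1. Then:

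- R2(X, T) = r² × corr(W1, T)²
- R2(X, W2) = r² × corr(W1, W2)²

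Simulation of 200,000 persons, weekly probability 0.8 of meeting the minimum until a single permanent stop, with the stopping curves of step 2. The value of r is an assumption, shown as a range.

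| r (assumed) | R2 against 52-week total | R2 against weeks 27-52, unadjusted |
|---|---|---|
| 0.3 | 0.07 | 0.02-0.04 |
| 0.5 | 0.19-0.21 | 0.07-0.11 |
| 0.7 | 0.37-0.40 | 0.13-0.22 |

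The ranges span the stopping curves.

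**4. Cross-check without a stopping curve**

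Give the two half-years equal variance and correlation ρ. The formulas become r²(1 + ρ)/2 for the total and r²ρ² for weeks 27-52. With r = 0.5 and ρ = 0, 0.3, 0.6:

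- total: 0.125, 0.163, 0.200
- weeks 27-52: 0.000, 0.023, 0.090

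The direction is the same: the overlap raises the apparent R2.

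**The case against.** **Start-of-study measures are predictors too, and weeks 27-52 do follow month 6.** This stands. A reader might infer that the model explains past exercise instead of predicting. The text does not support that; the model does both, and its accuracy figure does not separate them.

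**The feature set is not fully fixed.** The article describes five learning scores and one total gain, which fits one IGT run, and the wording about change is in the sentence that states the aim. A reader might conclude that the model can never be applied before month 6; that is an inference. Still, the aim names change and a 6-month span, every instrument is repeated at month 6, and nothing excludes those measures. The article itself states both windows, so this is not detail left to a fuller plan.

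**Reverse influence is not shown for every instrument.** This stands. The Introduction reports Type D as stable over 3 months and not dependent on mood or health status. No section says that exercise alters IGT performance. Status of change also covers intention and counts only planned activity, so it is not simply a copy of the target.

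**The illustration can be made to look too strong.** This stands. After adjustment for weeks 1-26 the marker in step 3 adds an R2 of 0.00 for weeks 27-52, but that is true by construction. The like-for-like contrast is the unadjusted column. In the same simulation an indicator of meeting the minimum in at least 2 of weeks 23-26 gives R2 0.65-0.72 on the total, yet also 0.49-0.57 on weeks 27-52, so much of that association looks forward.

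**Gym dropout may not describe Fitbit owners.** True, but step 1 does not depend on it.

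**Clustering is unsupervised.** True; the target does not enter the formation of clusters, only their later comparison with adherence.

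**Conclusion.** The concern holds in a limited form. About 26 of 52 target weeks precede the month-6 predictors and up to about 13 precede the first IGT. That follows from the stated windows and needs no assumption beyond counting 12 months as 52 weeks. Accuracy against the 52-week total therefore cannot be read as ability to identify in advance who will give up.

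The documents support reverse influence for status of change and self-efficacy, not for Type D or the IGT. A reader might infer that all predictors are contaminated or that a good fit would be wholly spurious; neither follows.

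The size of the bias in this study is unknown. The R2 ranges of 0.07-0.40 and 0.02-0.22 rest on assumed correlations of 0.3-0.7, a weekly probability of 0.8, one permanent stop and gym-member stopping curves. They show that the overlap can matter; they do not estimate it.

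**What to change.** State in Data Analysis and Computational Modeling that every predictor must be measured before its target period begins. Then:

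1. **Primary model.** Use start-of-study questionnaires plus the first IGT, and sum the weekly score only from a fixed point after the first IGT window, for example from month 3 (52 − 13 = 39 weeks). Alternatively, use start-of-study questionnaires alone for the full 52-week total.
2. **Secondary landmark model at month 6.** Month-6 levels and changes predict the weeks 27-52 score, with the weeks 1-26 score as a covariate.
3. **Clusters.** Those based on changes may stay, since they are a stated aim. Label their relation to the full 12-month total descriptive, not predictive.

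This is a change of analysis wording and needs no new data. The price is a shorter target period, probably a lower R2, and possibly many zero scores in weeks 27-52: about 86% on the first gym study's figures, or about 27-34% on the second's under constant hazard. With 200 participants planned, the first of these would leave the landmark model little to work with, and the plan should say so.

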### Making Predictions and Clustering

It is apparent that the numerical predictor variables are measured at different scales; therefore, a standardization process is necessary to make the numerical features identical regarding the range. *Z* score normalization that scales the value while considering the SD will be adopted in this case. Finally, a list of regression algorithms in machine learning will be applied to the cleaned data set, in which we characterize each participant with a vector of a certain length. The possible algorithms include linear regression, rigid regression, lasso regression, and neural network regression.

In addition, unsupervised learning algorithms that can work independently to discover patterns and information will be applied to the data set to identify potential behavioral phenotypes. The K-means clustering algorithm, one of the simplest unsupervised learning algorithms, can be used to solve this problem.

### Risks

Participation in this study presents no identifiable risk to the participants.

## Results

This study was funded by the Irish Research Council as part of an employment-based PhD scholarship. Ethics approval was obtained from Dublin City University in December 2020. At manuscript submission, study recruitment was pending. The expected results will be published in 2022.

## Discussion

### Overview

The rationale for this study is to determine whether data from decision-making games and personality traits could predict individuals most likely to give up on self-determined physical activity goals. The ability to identify the digital persona of those most likely to abandon exercise goals has significant value to those involved in developing targeted support to encourage and adhere to fitness goals.

### Methodological Limitations

#### Recruitment

Participants will not be incentivized to join the study, and as such, it may be challenging to reach the recruitment goals. A rolling strategy will be adopted with regular push notifications to social media and a dedicated study page established on Facebook to maximize recruitment. These pages will have details of the study, the app, and a YouTube instructional video.

#### Loss of Fitbit Data

All Fitbit devices have a finite internal memory, and intraday data are stored for 5 to 7 days, depending on the tracker (daily totals are generally retained for 30 days). If participants do not regularly synchronize their devices, the data can be overwritten.

Participants may fail to complete the required number of tests in the IGT to facilitate parameter modeling and derive the required insights.

Depending on the number of participants recruited for the study, the application of deep learning approaches may be limited owing to the participant numbers and may result in overfitting.

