### Study Interventions

#### Study App

The study app was developed by Dublin City University (AthenaCX, DCU). It allows researchers to rapidly design and deploy mobile experience sampling apps (iOS and Android), including integrated consenting and wearable data collection devices. This will provide the participants with a study overview in the form of plain language statements and privacy statements and facilitate the participants e-consent into the study. The app was designed to ensure that subjects have read the study details and consented to the study before completing the study assessments (Multimedia Appendix 1 includes a text sample from the plain language statement and informed consent in the mobile app). The participants have the right to withdraw from the study at any time. The app will be used to deliver the assessments and provide a link to the decision-making game. Push notifications will be sent to the participants during the study, requesting them to complete the assessments at the required time intervals, as detailed below.

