#### Fitbit

The use of fitness trackers in this study will facilitate the objective assessment of the participants’ activity patterns and behavioral changes in exercise. It will also enable the identification of individuals who already have a well-established exercise regime. A BYOD approach will be used, and data from each participant’s Fitbit will be captured. Fitbit devices are a range of physical activity trackers and smartwatches that combine integrated accelerometers and photoplethysmograph sensors to measure motion and heart rate. Proprietary algorithms convert the accelerometer data into sleep and activity patterns. Fitbit devices use Bluetooth low energy technology to synchronize with the individual’s mobile device and produce various metrics, including step count, floors climbed, distance covered, calories burned, active minutes, sleep time and stages, and heart rate. In this study, a high-frequency intraday data will be collected using a web-based application programming interface. These data are highly granular and include 1 minute and 15 minutes for activity and 1 second and 1 minute for heart rate.

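### The article does not say whether weekly exercise minutes come from intraday data (kept 5 to 7 days) or daily totals (about 30 days), and it scores lost time as nonadherence

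*Protocol article*

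**What the plan says.** All references are to the protocol article.

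- **Feed.** The Fitbit section states: "In this study, a high-frequency intraday data will be collected using a web-based application programming interface". Activity is taken at 1 and 15 minutes. The same section lists the metrics that the device produces: "step count, floors climbed, distance covered, calories burned, active minutes, sleep time and stages, and heart rate". It does not say whether active minutes will be taken as intraday records or as daily totals.
- **Target variable.** Data Analysis and Computational Modeling says: "We will mainly rely on the data set of activity patterns and the step counts". The weekly requirement is that "active periods should consist of 150 minutes of moderate-intensity brisk walking or 75 minutes of vigorous-intensity jogging or running over the course of a week". The scoring rule is: "If the participant completes this minimum exercise in a particular week, their adherence score for this week will be 1; otherwise, the score is 0". Weekly scores are then summed. No resolution is named, and there is no category for a week that was not fully observed.
- **Memory.** Loss of Fitbit Data, under Methodological Limitations, says that "intraday data are stored for 5 to 7 days, depending on the tracker (daily totals are generally retained for 30 days", and adds: "If participants do not regularly synchronize their devices, the data can be overwritten". No countermeasure is given.
- **Contacts.** The Study App section says: "Push notifications will be sent to the participants during the study, requesting them to complete the assessments at the required time intervals". The questionnaires fall at the start and at 6 months, and the gambling task falls within the first 3 months and at 6 months. Data capture runs for 12 months. The only later message described is the closing thank-you.

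**The concern.** These statements do not fit together. The feed described is the short-lived one. A record that lasts several times longer is named, but the article does not say it will be used. None of the described contacts is meant to make participants sync. The scoring rule then treats minutes that were overwritten in the same way as minutes that were never done.

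The summed weekly score is the quantity that every prediction model in the study is meant to predict. If it partly reflects tracker memory and sync habit, a model may partly learn who syncs instead of who keeps exercising. Participants bring their own trackers, so memory length can differ between them. Overwritten data cannot be recovered afterwards, so the source and the rule need to be fixed before data accrue.

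**Working it through.** The article derives no figure on this point, so there is none to reproduce. The check is a count of days.

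**Inputs from the article.** Intraday memory *m* is 5 to 7 days, and daily totals last about 30 days (Loss of Fitbit Data). The threshold is 150 moderate minutes a week (Data Analysis and Computational Modeling). Twelve months of capture (Recruitment) give about 52 weekly scores.

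**Assumptions.** The participant syncs every *s* days. Four moderate-intensity patterns are tried, each meeting the threshold every week, so the true score is 52 of 52: 5×30 min and 3×50 min on alternate days (both exactly 150), 7×30 min (210) and 5×60 min (300). A lost day contributes no minutes, which is how the scoring rule works when there is no missing category.

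**Step 1: days lost.** Days lost per sync cycle = max(0, *s* − *m*).

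| Sync every | *m* = 5 | *m* = 6 | *m* = 7 |
|---|---|---|---|
| 7 days | 2 (29%) | 1 (14%) | 0 |
| 10 days | 5 (50%) | 4 (40%) | 3 (30%) |
| 14 days | 9 (64%) | 8 (57%) | 7 (50%) |

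**Step 2: score with weekly sync.** The lost days fall on the same weekdays every week. A participant at the minimum scores 1 only if every lost day is a rest day. Averaging over the seven alignments of sync day and exercise days:

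- *m* = 5, 5×30: the two consecutive lost days must be the two rest days, which happens in 1 of 7 alignments. 52 × 1/7 = 7.4.
- *m* = 5, 3×50: there is only one pair of consecutive rest days. 52 × 1/7 = 7.4.
- *m* = 6, 5×30: 2 rest days of 7. 52 × 2/7 = 14.9.
- *m* = 6, 3×50: 4 rest days of 7. 52 × 4/7 = 29.7.
- *m* = 7: nothing is lost, and the score is 52.
- Above the minimum with *m* = 5: 210 − 2×30 = 150, and at worst 300 − 2×60 = 180. Both still meet the threshold, so the score is 52.

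The values 7.4 to 29.7 are averages over alignments. With fully fixed habits, one participant would score either 0 or 52.

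**Step 3: longer sync intervals.** This is the same count over 52 weeks, averaged over alignments, with ranges across *m* = 5 to 7 and the two patterns in each group:

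| Sync every | At the 150-min minimum | Above it (210 or 300 min) |
|---|---|---|
| 10 days | 2.2 to 12.6 of 52 | 15.6 to 40.9 of 52 |
| 14 days | 1.6 to 9.0 of 52 | 11.1 to 26.0 of 52 |

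**Step 4: the longer-lived record.** With daily totals, max(0, 28 − 30) = 0, so no day is lost and the score is 52 at every interval tried up to 28 days. Intraday data synced at least every 5 days also give 52.

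**The case against.** The strongest reply is that the article never says the minutes come from intraday records. It lists active minutes as a device metric and mentions the 30-day totals, so daily totals may be what is intended. That is correct, and it is why the point is conditional. It does not dispose of the point, because intraday is the only feed described and the scoring section leaves the choice open.

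Second, a reader might infer that everyone who syncs weekly or less often loses part of every week, or that an adherent participant scores 0 throughout. The article's own range does not support either reading. A 7-day memory with weekly sync loses nothing. A score of 0 in every week whatever the alignment needs, for example, a 5-day memory, weekly sync, exercise spread evenly over all seven days and no margin (150 × 5/7 = 107 minutes).

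Third, no sync frequency is given. The tracker syncs by Bluetooth with the participant's own phone, so syncing need not depend on study contact. How many participants would be affected is therefore unknown, and bias that differs by device or engagement is possible but not shown.

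Fourth, one might claim that a partly overwritten week would pass as valid. The article does not say whether an overwritten day reads as zero or as absent. If it reads as absent, a day-level completeness check would find it.

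Finally, the loss is disclosed as a limitation, and sync procedures or completeness rules may well sit in a fuller document. Their absence from the article is not the fault raised here. The fault is that the stated rule sends every week not shown to meet the threshold to 0, and that disclosure does not change what the rule does.

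**Conclusion.** The point holds in conditional form. If the weekly minutes are taken from intraday data, the rule as stated can score an adherent participant as nonadherent when syncing is less frequent than the tracker's memory. For someone exactly at 150 minutes with weekly sync, the average falls from 52 to about 7 with a 5-day memory and to 15 to 30 with a 6-day memory. It does not fall with a 7-day memory, and participants at 210 or 300 minutes keep 52 at that interval. With sync every 10 or 14 days the loss reaches all memory lengths in the stated range and also those above the minimum.

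These sizes rest on assumed sync intervals and exercise patterns. They show what the rule can do and do not forecast how often it will happen. If daily totals are intended, the loss disappears for syncing up to about monthly, and one sentence saying so would settle the matter of source. The failure to separate lost from inactive time would remain for longer gaps.

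**What to change.** 1. **Name the source.** State that the weekly score is derived from daily totals of active minutes where these are available by intensity, with intraday data for secondary detail. The article does not confirm that retained totals include active minutes or separate moderate from vigorous, which the 150/75 rule needs, so this must be checked first.
2. **Separate missing from inactive.** Score a week 1 if its observed days reach the threshold. If any day is missing and the observed days fall short, record the week as incomplete, not 0. Base the adherence score on observed weeks, for example as a proportion instead of a sum.
3. **Optional.** Have the existing app send a neutral, automatic sync reminder, with no exercise content, when no sync has been received within the shortest memory window, for the full 12 months.

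The cost is a few sentences in the target definition and, if adopted, one push rule. Daily totals give up within-day timing, which the score does not use. Under item 2 an incomplete week can count only as 1 or drop out, which tilts the score upward, so a sensitivity analysis on complete weeks only and a report of incomplete weeks per participant should go with it. The reminder adds mild extra contact to an observational study of exercise decay. Recruitment was still pending when the article was submitted, so these changes could be made before any data were lost.
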